#### 2.10.2. Secondary Mental Health Outcome Measures

Disordered eating behaviors: The SCOFF questionnaire [74] will be used to detect the possible presence of disordered eating. This five-item tool assesses core behaviors and attitudes related to food, weight, and body image. Responses will be recorded as “yes” or “no”, with a score of two or more indicating a probable risk of an eating disorder. The Spanish version of the SCOFF questionnaire demonstrated excellent psychometric properties among youth populations; a cutoff of more than two positive responses provided a sensitivity of 97.7% and a specificity of 94.4% for the detection of eating disorders [74].

Body image perception: Body image dissatisfaction will be assessed using the Standard Figural Stimuli (SFS), which was originally developed by Stunkard et al. [75] and subsequently validated in Spanish-speaking young populations by Rueda-Jaimes et al. [76]. The SFS consists of nine male silhouettes and nine female silhouettes arranged in ascending order of body mass index, with the numeric values concealed from the participants. Each student will first choose the figure they believe best represents their current body shape and then the figure they consider most desirable. Body image dissatisfaction is quantified as the numerical difference between the selected current and ideal silhouettes.

Resilience: The Spanish adaptation of the CD-RISC-10 [77], a shortened version of the Connor-Davidson Resilience Scale [78], will be used to assess psychological resilience. This instrument comprises ten items, with each item rated on a five-point Likert scale ranging from 0 to 4. The total scores range from 0–40, with higher scores reflecting greater levels of resilience. The scale provides a reliable and efficient measure of participants’ ability to cope with stress and adapt to adversity. This scale has shown good internal consistency (Cronbach’s α = 0.85) in young adults [77].

Health-related quality of life: Health-related quality of life (HRQoL) will be assessed using the 12-item Short Form Health Survey (SF-12), a validated instrument providing a reliable measure of perceived health status [79]. The twelve items assess functional status, well-being, and overall health across eight domains. Responses will be scored using standard algorithms [79] to generate a Physical Component Summary (PCS) and a Mental Component Summary (MCS), both of which are standardized to a mean of 50 and a standard deviation of 10. Higher scores indicate better perceived HRQoL. The SF-12 demonstrated acceptable reliability for both physical and mental component scores (reliability coefficients ≈ 0.78–0.85) [80].

Sleep quality: Sleep quality will be assessed via the Pittsburgh Sleep Quality Index (PSQI) [81], a widely validated self-report questionnaire designed to evaluate overall sleep quality over the past month. The PSQI includes 19 items that generate seven component scores: subjective sleep quality, sleep latency, sleep duration, habitual sleep efficiency, sleep disturbances, sleep medication use, and daytime dysfunction. Each component is scored from 0 to 3, with higher scores indicating poorer sleep quality. The sum of the component scores yields a global score ranging from 0 to 21, where a score greater than 5 is indicative of poor sleep quality. The Spanish version of the PSQI showed good psychometric properties (Cronbach’s alpha = 0.72) across diverse populations, including young adults and university students [82].

#### 2.10.3. Potential Confounding, Mediating, and Moderating Factors

Socioeconomic level, demographic features, and medical history: Family socioeconomic status (SES) will be derived from data concerning maternal and paternal education and occupation. Parental education will be categorized into three levels: primary (incomplete primary education or functional illiteracy), secondary (completed primary and secondary/high school education), and university (bachelor’s degree or postgraduate qualification). Paternal and maternal occupation will be classified into five hierarchical categories: (1) supervisor/manager or self-employed with ≥10 employees; (2) supervisor/manager or self-employed with <10 employees; (3) self-employed without staff; (4) unqualified staff and unskilled workers; and (5) household duties, unemployed, or other. A composite SES index will be subsequently calculated by combining parental education and occupation metrics. This index, which is based on the scale proposed by the Spanish Society of Epidemiology, categorizes family SES into five distinct groups: lower, upper lower, lower middle, upper middle, and upper [83].

Participants will complete a self-administered questionnaire to provide information on medication and family history of mental or cardiovascular disorders, as well as demographic characteristics, including birth date, sex at birth, gender, migrant status, marital status, type of housing, and, for female participants, menstrual status, pregnancy, and breastfeeding.

Anthropometric measures and body composition: Body weight and other body composition variables, such as body fat percentage, fat mass and lean mass, will be assessed using a Tanita MC-780 MA-N analyzer (Tokyo, Japan). Height will be measured to the nearest 0.1 cm using a wall-mounted stadiometer (Seca^®^ 213, Hamburg, Germany). Body composition and height will be measured in duplicate, and the average of the two measurements will be used for analysis. The body mass index (BMI) will be calculated using the Quetelet formula (weight [kg]/height [m^2^]). Waist circumference will be measured by the average of three determinations at the midpoint between the lowest rib and the superior border of the iliac crest following normal exhalation, with participants removing belts or clothing that could alter body shape without applying external pressure. Additionally, dual-energy X-ray absorptiometry (DXA) will be used to assess lean mass, fat mass, bone mineral content (kg), and bone mineral density (g/cm^2^) (Lunar iDXA, GE Medical Systems, Madison, WI, USA). All scans were processed using Physician’s Viewer, APEX System Software Version 3.1.2 (Worthington, MN, USA), and analyses were performed with enCoreTM 2008 software, version 12.30.008 (GE Healthcare, Madison, WI, USA). Instrument accuracy will be verified daily prior to each scanning session using the GE Lunar calibration phantom, following the manufacturer’s recommendations. All measurements will be obtained at high resolution by a trained researcher using a standardized protocol.

Food consumption and nutrient intake: Two methods will be used to assess dietary behavior. First, a 137-item semiquantitative food frequency questionnaire (FFQ) from the PREDIMED Plus study [84] will be administered to assess participants’ habitual dietary intake over the previous year. This FFQ has demonstrated good reproducibility (ICC: 0.63–0.90) and acceptable validity (ICC: 0.40–0.84) for food group assessment in an elderly Spanish Mediterranean population [84]. The validated tool captures the frequency and portion size of a wide variety of foods, including fruits, vegetables, legumes, cereals, dairy products, meats, fish, eggs, nuts, oils, and beverages such as wine, coffee, and soft drinks. The data collected will allow the estimation of energy intake, macronutrients (carbohydrates, proteins, fats), micronutrients (vitamins and minerals), fiber, and bioactive compounds such as polyphenols. Food composition data will be collected from the Spanish Food Composition Database [85] to derive nutrient compositions and estimate total energy intake.

Adherence to the Mediterranean diet: Adherence to the Mediterranean diet (MedDiet) and its specific components will be measured with the Mediterranean Diet Adherence Screener (MEDAS), a Spanish-validated questionnaire that consists of 14 questions [67]. The MEDAS has demonstrated acceptable concurrent validity against a validated FFQ (r = 0.52, ICC = 0.51) in Spanish adults at high cardiovascular risk [86]. The participants will be provided with the MEDAS to complete a tablet, including 12 questions about the frequency of food intake (i.e., olive oil, vegetables, fruit, red meat, animal fats, carbonated beverages, red wine, fish/seafood, nuts, commercial food, and traditional sauces) and 2 questions about food intake habits (i.e., preferred cooking fat used and type of meat consumed) considered characteristic of the Spanish MedDiet. Each question offers two response options, with corresponding scores of 0 (no adherence to the MedDiet component) or 1 (adherence to the MedDiet component).

Specifically, participants are awarded 1 point for adhering to specific dietary components, which includes the use of olive oil as the primary source of fat for cooking, which favors white meat over red meat and consumes the following on a daily or weekly basis: (i) 4 or more tablespoons (~13.5 g per tablespoon) of olive oil per day; (ii) 2 or more servings of vegetables per day; (iii) 3 or more servings of fruit per day; (iv) less than 1 serving of red meat or sausages per day; (v) less than 1 serving of animal fat per day; (vi) less than 1 cup (~100 milliliters) of sugar-sweetened beverages per day; (vii) 7 or more servings of red wine per week; (viii) 3 or more servings of pulses per week; (ix) 3 or more servings of fish per week; (x) fewer than 2 commercial pastries per week; (xi) 3 or more servings of nuts per week; and (xii) 2 or more servings per week of a dish featuring a traditional sauce made of tomatoes, garlic, onion, or leeks sautéed in olive oil.

The final score is the sum of each item (0–14), where a higher score indicates higher MedDiet adherence. The MEDAS score can be categorized as follows: scores < 9 indicate low adherence to the MedDiet, and scores from 9 to 14 indicate good adherence to the MedDiet [87].

Screen time: Screen time will be assessed using a self-administered questionnaire in which participants will report the number of hours they usually spend watching television, using a mobile phone, computer (for work), or other electronic devices (for leisure use) on both weekdays and weekends.

Social media addiction: Social media addiction will be measured using the short-form Social Media Addiction Scale (ARS-6), a six-item self-report instrument designed to capture core components of addictive behavior, including salience, mood modification, tolerance, conflict, and relapse, adapted to the social media context. The participants respond on a five-point Likert scale ranging from “never” to “always”, with higher scores indicating a greater risk of social media addiction [88]. This scale has been validated in adolescent and university populations, demonstrating excellent psychometric properties, including high internal consistency (Cronbach’s α = 0.923–0.950; McDonald’s ω = 0.916–0.960) [88,89].

Problematic substance use: The Alcohol, Smoking and Substance Involvement Screening Test (ASSIST) [90] will be administered to evaluate participants’ risk of substance-use disorders and associated health, social, and legal consequences. This instrument, developed by the World Health Organization (WHO), enables the assessment of involvement across multiple substance categories (including alcohol, tobacco, and illicit drugs) by means of structured items addressing lifetime use, frequency of use in the past three months, craving intensity, failed obligations, and concerns expressed by others. Risk classifications follow the original ASSIST thresholds: for alcohol, 0–10 points indicate low risk, 11–26 points indicate moderate risk, and 27 points or more indicate high risk; for tobacco and all other substances, 0–3 points indicate low risk, 4–26 points indicate moderate risk, and 27 points or more indicate high risk. The Spanish version of the ASSIST has demonstrated adequate psychometric properties, with high internal consistency (Cronbach’s α = 0.86–0.97 across substances) [91].

Physical activity: The short form of the International Physical Activity Questionnaire (IPAQ) [92] will be used to quantify participants’ physical activity levels. This seven-item instrument provides a comprehensive assessment of vigorous-intensity activity, moderate-intensity activity, walking, and sedentary time during the preceding week. Following the official scoring protocol, reported activity durations for each activity category will be converted into metabolic equivalent of task minutes per week (MET-min/week), enabling classification of individuals into low, moderate, or high physical activity levels. Low activity level includes individuals who do not meet moderate or high criteria (inactive); moderate level includes those engaging in ≥3 days of vigorous activity (20 min/day), ≥5 days of moderate-intensity activity or walking (30 min/day), or any combination totaling ≥600 MET-min/week; high level includes those with ≥3 days of vigorous activity totaling ≥1500 MET-min/week, or ≥7 days of any combination of walking, moderate, or vigorous activity totaling ≥3000 MET-min/week. The IPAQ has demonstrated a good reliability coefficient for total physical activity (r = 0.82, *p* < 0.05), vigorous activity (r = 0.79, *p* < 0.05), moderate activity (r = 0.83, *p* < 0.05), and time spent walking (r = 0.73, *p* < 0.05) within Spanish-speaking adult populations, including samples of university students [92,93].

Muscular strength: Upper-body muscle strength (handgrip strength in kilograms) will be assessed following a 2 min warm-up consisting of joint mobilization and static stretching. The maximal isometric handgrip strength will be measured using a calibrated dynamometer (TKK 5401 Grip-D, Takeya, Tokyo, Japan) [94] with the grip adjusted to the participant’s dominant hand size, ensuring that the second joint of the index finger forms approximately a right angle. Hand size, defined as the distance from the tip of the thumb to the fifth digit at maximum extension, will be measured prior to testing.

The participants stand upright with their feet’ shoulder width apart, with their arms extended and slightly away from the body and perform two maximal squeezes per hand for 3–5 s, with 10 s rest intervals between attempts. Prior to testing, the procedure and grip technique will be demonstrated, and participants will perform practice squeezes to ensure proper technique. Excessive movements are prohibited, and maximal effort is encouraged throughout. Handgrip strength will be recorded in kilograms, with the highest value used for analysis.

The standing long jump test will be used to assess lower-body muscular strength [95]. The participants stand behind a designated line with their feet approximately shoulder width apart and jump forward with both feet simultaneously, aiming to achieve maximum distance. The distance will be measured in centimeters from the starting line to the posterior edge of the heels upon landing. Each participant will perform three attempts, and the longest jump will be recorded for subsequent analysis.

Self-reported fitness: Additionally, physical fitness will be assessed using the International Fitness Scale (IFIS) [96,97], a validated self-report questionnaire. The participants will be asked to rate their perceived overall fitness, cardiorespiratory fitness, muscular strength, speed/agility, and flexibility on a five-point Likert scale from “very poor” to “very good”. The IFIS has demonstrated reliability and validity in Spanish-speaking university populations, providing a feasible tool to evaluate subjective fitness levels with a Cronbach’s alpha of 0.90 [98] and an intraclass correlation coefficient of 0.947 [99].

Blood pressure: Blood pressure will be measured following standardized procedures. The participants will be instructed to empty their bladder prior to measurement and will then rest in a seated position for 5 min before assessment. Two BP measurements will be taken on the same arm with a 3 min interval between readings. A third measurement will be obtained if (1) the systolic blood pressure (SBP) in any measurement exceeds 130 mmHg or if (2) the difference between the two measurements is >10 mmHg for either SBP or diastolic blood pressure (DBP). The average of the two valid measurements will be used for analysis. Measurements will be obtained using a validated automated device (OMRON HEM-907, Omron Healthcare UK Ltd., Milton Keynes, UK), and the mean of the two readings will be used for analysis.

Blood biochemical parameters: Fasting blood samples will be collected from the cubital vein between 08:15 and 09:00 h following at least 12 h of overnight fasting. These samples will be used to determine basic hemograms; lipid profiles, including total cholesterol, high-density lipoprotein cholesterol (HDL-c), low-density lipoprotein cholesterol (LDL-c), and triglycerides; glycemic metabolism markers, including fasting serum glucose, insulin, and glycated hemoglobin (HbA1c); selected vitamins (vitamin D, vitamin E, vitamin B12, and folic acid); essential minerals (iron and magnesium); and inflammatory markers, including high-sensitivity C-reactive protein (hs-CRP) and interleukin 6 (IL-6). All analyses will be performed using standardized laboratory methods under strict quality control procedures to ensure accuracy and reliability.

Brain-derived neurotrophic factor (BDNF): BDNF has received increasing attention because of its potential correlation with mental health [28]. Blood levels of BDNF will be measured to assess neurotrophic support in participants. Venous blood samples will be collected in tubes to separate the serum with gel following an overnight fast to minimize circadian and dietary variability. The samples will be immediately centrifuged at 3000 g for 10 min at ambient temperature, and the serum will be aliquoted and stored at −80 °C until analysis. BDNF concentrations will be quantified using a commercially available enzyme-linked immunosorbent assay (ELISA) kit (Aviscera Bioscience, Santa Clara, CA, USA, INC SK00752-01C) following the manufacturer’s protocol. All assays will be performed in duplicate, with intra-and inter-assay coefficients of variation maintained below 10%. The results will be expressed in pg/mL and analyzed as continuous variables in subsequent statistical analyses.

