### 2.11. Data Management and Statistical Analysis Plan

The principal investigator will have exclusive responsibility for the data and will retain an offline copy on a secure hard drive. The anonymized data will be stored in an open-access repository (Zenodo.org) and may be shared with other researchers upon reasonable request.

The initial analytical approach will comprise descriptive statistics and data visualization to perform an exploratory assessment of the dataset, including an evaluation of bivariate associations between the predictor variables (nut consumption doses) and the outcome variables (mental health parameters). This stage will assess potential baseline differences among the three groups (CG, IG-30, and IG-60).

Subsequently, assumptions of normality and homoscedasticity for the outcome variables will be examined to ascertain the suitability of employing a repeated-measures mixed-effects model to characterize the intervention relationship between nut consumption and mental health indicators. Interpretation will focus on the magnitude and statistical significance of the fixed effects coefficients, thereby determining whether nut consumption is associated with changes in mental health outcomes and whether these associations vary across study intervention groups.

The role of BDNF will also be analyzed, examining associations between BDNF changes and mental health measures through correlation analysis at each timepoint, mediation analyses using structural equation modeling to test whether BDNF mediates the relationship between nut consumption and mental health, including cognitive improvements, and dose–response analyses across study arms. Secondary exploratory analyses will include responder analyses (BDNF increase), time-course analyses using linear mixed models, and interaction analyses examining moderators such as baseline BDNF levels and mental health status. All BDNF-cognition analyses will be designated as secondary/exploratory with appropriate adjustments for multiple comparisons and covariates, including age, sex, baseline cognitive performance, physical activity, and dietary quality.

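### The five ordered parental occupation classes have no place for qualified employees without supervisory duties, so the occupation component of SES ranks them below unskilled workers

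*Protocol article*

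**What the plan says.** Protocol article, section 2.10.3, paragraph on socioeconomic level. The starting point is: "Family socioeconomic status (SES) will be derived from data concerning maternal and paternal education and occupation". Parental education has three levels, with university at the top. For occupation: "Paternal and maternal occupation will be classified into five hierarchical categories". The top rank is "1) supervisor/manager or self-employed with ≥10 employees". Two further ranks for people who run or own a business follow, namely "2) supervisor/manager or self-employed with <10 employees; (3) self-employed without staff". The article then closes its scale with two ranks for all remaining parents: "4) unqualified staff and unskilled workers; and (5) household duties, unemployed, or other".

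The two components are then merged: "A composite SES index will be subsequently calculated by combining parental education and occupation metrics". On its origin: "This index, which is based on the scale proposed by the Spanish Society of Epidemiology, categorizes family SES into five distinct groups". The article gives no weights, scores or cut-offs for the index. Table 1 lists SES as self-reported on a tablet.

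**The concern.** The list is presented as a complete ordered scale: the text announces five classes and then numbers and defines five. Yet the qualified employee who supervises nobody, a common kind of parent, is not described by any of the first four. The only class left is the residual one, which shares the bottom rank with the unemployed and those doing household work.

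If the tablet questionnaire follows this list, the coding fault is directional: it moves qualified employees down, never up. It also mixes them with a very different group. If occupation is stored only as one of these five codes, the mixture cannot be separated after collection. SES is one of the variables grouped under potential confounding, mediating and moderating factors, so a distorted version would weaken the description of the sample and any analysis that adjusts for SES or looks for effect modification by it.

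**Working it through.** The plan states no figure to reproduce here. The check is whether the printed classes are exhaustive and how they are ordered, followed by an illustration on stated assumptions.

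**Step 1: place a qualified, salaried, non-supervisory employee.**

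| Class (section 2.10.3) | Does this parent fit? |
|---|---|
| 1 and 2 | No: neither manager or supervisor, nor self-employed with staff |
| 3 | No: not self-employed |
| 4 | No: neither unqualified nor unskilled |
| 5 | Only through its residual wording |

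An unskilled labourer goes to class 4 and an unemployed parent to class 5. The qualified employee therefore ranks below the first and level with the second. This follows from the text alone.

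**Step 2: can the shift in the index be computed?** No. The weights and cut-offs are not printed, and the source scale is not at hand. What follows is an illustration only. Assumptions: education and occupation are each scaled 0 to 1 with equal steps, and the parent's composite is (1 − w) × education + w × occupation, with w between 0.25 and 0.75.

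*Size of the shift.* Insert a class for qualified employees between classes 3 and 4. In the resulting six-class list the scores are 1, 0.8, 0.6, 0.4, 0.2 and 0, so this parent should score 0.4 instead of 0. The composite is too low by 0.4w: 0.4 × 0.25 = 0.10 to 0.4 × 0.75 = 0.30. With five equal bands of width 0.2, that is 0.5 to 1.5 bands. Averaging with a correctly coded second parent halves it, to 0.25 to 0.75 bands.

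*Does education offset it?* In the printed five-class list, class 4 scores 0.25 and class 5 scores 0. At w = 0.5:

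- university-educated qualified employee, class 5: 0.5 × 1 + 0.5 × 0 = 0.50
- unskilled worker, university education: 0.5 × 1 + 0.5 × 0.25 = 0.625
- unskilled worker, secondary education: 0.5 × 0.5 + 0.5 × 0.25 = 0.375
- unskilled worker, primary education: 0.5 × 0 + 0.5 × 0.25 = 0.125

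At equal education the order is reversed. Against an unskilled parent with less schooling it is not. For the graduate to fall below an unskilled parent with secondary education, (1 − w) < 0.5(1 − w) + 0.25w is needed, that is w > 2/3. So the offset is real but depends on the unstated weight.

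**Step 3: how many families could be touched?** The article gives no occupational distribution. Assume a share s of 30% to 60% of parents are qualified non-supervisory employees. If the two parents are independent, at least one is affected in 1 − (1 − s)²: 1 − 0.7² = 51% to 1 − 0.4² = 84% of families. Both are affected in s²: 9% to 36%. Parents' occupations are likely to be positively correlated, which lowers the first range. At perfect correlation it falls to s itself, 30% to 60%. These figures count families with an affected occupation code, not families placed in the wrong SES group. The latter cannot be derived from the article.

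**Step 4: where does SES enter the analysis?** Randomization is stratified by sex only (section 2.6). The covariates named for the BDNF–cognition analyses in section 2.11 are "including age, sex, baseline cognitive performance, physical activity, and dietary quality", without SES. Section 2.12.2 adds examination period and season to the mixed models, again without SES. Parental SES is fixed before randomization, so miscoding it is unrelated to arm.

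**The case against.** The strongest reply is that a journal article condenses. The index is attributed to a published scale, and the questionnaire and coding manual are not shown. Class 4 reads almost as a repetition of itself, which would fit a wording slip or a lost label. That the trial would really code a salaried teacher in the residual class is an inference from the printed list. This stands in part: the document cannot tell a coding fault from a drafting fault. But it is not a detail left to a fuller document. The article states five classes and defines each, and as defined they mis-rank these parents. Either the coding or the published definition has to change. Citing the source scale does not tell a reader where these parents go.

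A reader might infer that the SES index as a whole is wrong, or that an SES-by-arm result could point the wrong way. The documents do not support either. The index also uses education, its scoring is not printed, and the illustration shows that the reversal need not carry through to the composite. No SES-by-arm analysis is planned by name. The examples given are baseline BDNF and mental health status in section 2.11, and diet, activity and fitness in the Discussion, whose list is left open.

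**Conclusion.** The point holds for the occupation component. The printed scale leaves out qualified or skilled employees without supervisory duties and, read literally, puts them at the bottom rank, below unskilled workers. This can pull the composite index down. The size of the shift is unknown. Half a band to one and a half bands per parent is an illustration that rests on equal steps, equal bands and an occupation weight of 0.25 to 0.75. The share of families affected rests on an assumed occupational mix.

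The consequence is modest. SES is not an outcome, not a stratification factor and not a named model covariate, so the randomized comparisons on the primary outcomes are not biased. What can suffer is the description of SES and any analysis that adjusts for it or examines it as a moderator. The change is still worth making, because the article precedes recruitment and a mixed bottom class may not be separable later.

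**What to change.** Before recruitment:

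- Reconcile the class list with the Spanish Society of Epidemiology scale that the article cites, and add or restore a class for qualified or skilled employees without supervisory duties, ranked above unskilled workers.
- Take the residual answer out of the ranked scale. Record it as a separate, unranked option with free text, so that it can be recoded to a class without knowledge of the arm.
- Do not treat the residual answer as the lowest rank, and do not simply set it to missing. Section 2.12.2 leaves covariates out of its missing-data handling, so those families could be lost from any SES-adjusted model.
- State the scoring rule of the composite, or refer to where it is given.

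The cost is one more answer option and one more derivation line, plus the recoding of a few free-text answers. No visit or procedure is added.
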